## Abstract

**Background:**

Plantar fasciopathy is a common cause of foot pain, accounting for 11 to 15 % of all foot symptoms requiring professional care in adults. Although many patients have complete resolution of symptoms within 12 months, many patients wish to reduce this period as much as possible. Orthotic devices are a frequently applied option of treatment in daily practice, despite a lack of evidence on the effectiveness. Therefore, the objective is to study the (cost)-effectiveness of custom made insoles by a podiatrist, compared to placebo insoles and usual care in patients with plantar fasciopathy in general practice and sports medicine clinics.

**Method/design:**

This study is a multi-center three-armed participant and assessor-blinded randomized controlled trial with 6-months follow-up. Patients with plantar fasciopathy, with a minimum duration of complaints of 2 weeks and aged between 18 and 65, who visit their general practitioner or sport physician are eligible for inclusion. A total of 185 patients will be randomized into three parallel groups. One group will receive usual care by the general practitioner or sports physician alone, one group will be referred to a podiatrist and will receive a custom made insole, and one group will be referred to a podiatrist and will receive a placebo insole. The primary outcome will be the change from baseline to 12 weeks follow-up in pain severity at rest and during activity on a 0–10 numerical rating scale (NRS). Secondary outcomes include foot function (according to the Foot Function Index) at 6, 12 and 26 weeks, recovery (7-point Likert) at 6, 12 and 26 weeks, pain at rest and during activity (NRS) at 6 and 26 weeks and cost-effectiveness of the intervention at 26-weeks. Measurements will take place at baseline and at, 2, 4, 6, 12 and 26 weeks of follow-up.

**Discussion:**

The treatment of plantar fasciopathy is a challenge for health care professionals. Orthotic devices are frequently applied, despite a lack of evidence of the effectiveness on patient reported outcome. The results of this randomized controlled trial will improve the evidence base for treating this troublesome condition in daily practice.

**Trial registration:**

Dutch Trial Registration:NTR5346. Date of registration: August 5^th^ 2015.

## Background

Plantar fasciopathy is a common cause of foot pain in both primary and secondary care. Plantar fasciopathy was formerly known as plantar fasciitis in literature. It typically affects middle aged or older women (40–60 years), with being overweight as a risk factor [1–3]. Besides this, plantar fasciopathy is also commonly seen in highly physically active people; plantar fasciopathy accounts for 8–10 % of all running related injuries [4]. Plantar fasciopathy accounts for approximately 11 to 15 % of all foot symptoms requiring professional care among adults and it has been estimated that a general practitioner (GP), with an average size practice, diagnoses around eight new patients each year [5, 6].

The etiology of plantar fasciopathy is poorly understood and is probably multifactorial [7, 8]. Histopathology studies have indicated that fasciopathy of the plantar fascia might be a possible cause of pain [9, 10]. Repetitive microtrauma and inflammation have been suggested as possible etiologic mechanisms, however these conclusions are mostly based on clinical experience and there is little evidence from research [11–13].

Plantar fasciopathy is characterized by pain over the anteromedial aspect of the inferior heel and the pain tends to increase after periods of inactivity or during weight bearing activities. The diagnosis can be made primarily based on symptoms and physical examination [7]. Patients often report low quality of life and reduced participation as their heel pain prevents them from performing simple every day activities [14, 15]. The clinical course of plantar fasciopathy is considered favorable as 80 % of patients will have a complete resolution of symptoms within 12 months [7]. Despite the favorable clinical course on the long term, many patients do expect and hope for short term pain relief and often multiple treatments are applied during the course of their complaints [7, 16].

The most commonly prescribed treatments include footwear modification, taping, stretching exercises, anti-inflammatory agents, Extra Corporal shock wave therapy (ESWT) and cortisone injections [7, 12]. Reviews conclude that most of these treatments have a role in the management of plantar fasciopathy although at different time points in the clinical course [7, 11–13, 17]. Despite the use of many different treatment strategies in plantar fasciopathy, there is insufficient evidence for the effectiveness of these treatments provided by high quality randomized controlled trials [12, 13, 18, 19].

It has therefore been suggested that treatment options should be offered to the patient in sequence, either based on objective patient criteria or based on the preference of the patient [12]. Different combinations of conservative treatments successfully manage 85–90 % of the cases of plantar fasciopathy [16]. Orthotic devices seem to be a frequently applied treatment option, despite a lack of evidence on the effectiveness [6, 16]. A clinical practice guideline from the American College of Foot and Ankle Surgeons recommends anti-inflammatory drugs (NSAIDs), stretching and prefabricated orthotics as the initial steps in the conservative treatment of plantar heel pain and prescription orthotic devices as a secondary treatment option [6]. Orthotic devices include a low risk intervention, they are relatively painless compared to other treatments, such as shock wave therapy or cortisone injections, and they have a working mechanism that influences on what are thought to be important biomechanical factors in the etiology of plantar fasciopathy. There are different theoretical models on the potential working mechanism of orthotic devices [20]. The most common theory is that orthotic devices optimize the biomechanical loading of the foot, specifically to decrease excessive pronation, to off-load the plantar fascia at its origin and to recreate the heel pad [21].

Orthotic insoles (custom made by a podiatrist) and prefabricated insoles belong to the most researched biomechanical treatments of plantar fasciopathy [12, 18, 19, 22]. However a Cochrane review on the effectiveness of insoles on foot pain concludes that there is insufficient evidence from high quality trials to support the effectiveness of orthotics in patients with plantar fasciopathy on different outcome measures such as pain, function and recovery [22]. Only one study included in this review compared the effectiveness of a custom made insole to a prefabricated insole (non-custom) and a sham insole (placebo) in patients with plantar fasciopathy. Both the custom-made and prefabricated insoles had slightly better outcomes on short term, but were not significantly different and both did not have beneficial effects on pain at 12 months [18].

To our knowledge there is no literature available on the cost-effectiveness of orthotic insoles for the treatment of plantar fasciopathy.

Given the favorability of treatment of plantar fasciopathy with insoles, the high estimated costs involved due to the custom-made nature and the insufficient evidence for this intervention, there is a need to conduct a high quality randomized controlled trial investigating the effectiveness of orthotic insoles on pain, function and recovery in patients with plantar fasciopathy.

### Objectives

The primary objective of our study is to examine the effectiveness of custom made insoles by a podiatrist, compared to placebo insoles and compared to usual care in general practice and sports medicine alone in patients with plantar fasciopathy in terms of pain.

The secondary objective of our study is to examine the cost-effectiveness of custom made insoles by a podiatrist, compared to usual care in patients with plantar fasciopathy.

## Methods

### Study design

The STAP-study is a multi-center three-armed armed participant and assessor-blinded randomized controlled trial with 6-months follow-up. STAP is an acronym for: Soles as Treatment Against Pain in feet. The reporting of the study protocol will follow CONSORT guidelines [23]. The study design and flow of participants is shown in Fig. 1. Participants will be recruited in general practice and sports medicine clinics, both accessible without referral. Those who are eligible and give written consent to participate will be randomly assigned to either the usual care group, the placebo insole group and the custom-made insole group. The study is funded by the Netherlands Organization for Health Research and Development (ZonMW) and the Dutch Association of Podiatrists (NVvP). The study design, procedures and informed consent procedure are in compliance with the Declaration of Helsinki, 7^th^ version, October 2013 [24]. The Medical Ethics Committee (number 2015–253) of the Erasmus Medical Centre in Rotterdam has approved this study. This permission includes the multi-centre nature of this study, i.e. approval was given to recruit patients at all sites.

**Fig. 1 Fig1:**
[figure not shown]
STAP study Flow chart

### Patient selection

Patients with plantar fasciopathy, characterized as pain at the medial hind foot, presenting themselves to a GP or sports physician, aged between 18 and 65 years and a minimal pain duration of 2 weeks are eligible for participation.

Participants will be excluded if they have recurrent complaints of plantar fasciopathy for more than 2 years, complaints caused by trauma, earlier treatment for plantar fasciopathy by a podiatrist or treatment with orthotics, suspected (by the GP or sports physician) (osteo)arthritis in the subtalar or talonavicular joint, suspected tarsal tunnel syndrome, suspected stress fractures, infections or tumors in the painful foot or presence of systemic diseases (such as Bechterew’s disease, psoriasis or multiple sclerosis). Patients who have no sufficient understanding of the Dutch language will also be excluded, since they will not be able to complete the questionnaires.

### Sample size

Based on the RCT of Landorf et al. (2006) [18] –pain score 63.4 (SD 21.5), with a difference in pain score of 10.5 (on a scale of 0–100) – it is estimated that with a power of 80 % and an alpha of 0.05 (two-sided), it is possible to detect an effect size of 0.5 with 10.5 points difference on the pain score between patients with a placebo insole and custom made insole with 63 patients in each study group. In addition, a larger difference is expected between the custom made insole group and the usual care group. With a 12-point difference and identical means and SDs, a total of 44 patients are needed per group. A Bonferroni correction will be performed for the secondary comparisons to the usual care group. Taking a loss to follow-up of 10 % into account, a total of 185 patients with plantar fasciopathy (69 in custom made group, 69 in placebo group and 47 in usual care group) will be included in the trial.

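### The size of the custom-versus-placebo comparison rests on an effect size rounded up from 0.488 to 0.5 and a slightly short loss allowance, so the unadjusted calculation gives about 77% power rather than 80%

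*Protocol article*

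**What the plan says.** The Sample size section of the protocol article takes its inputs from an earlier randomised trial of insoles: "pain score 63.4 (SD 21.5" and "with a difference in pain score of 10.5", both on a 0–100 scale. It sets the error rates "with a power of 80 % and an alpha of 0.05 (two-sided". From these it states that "it is possible to detect an effect size of 0.5 with 10.5 points difference on the pain score" between placebo and custom made insoles "with 63 patients in each study group". For custom made insoles against usual care it assumes 12 points with the same SD and gives 44 per group.

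It then allows for 10% loss and arrives at 185 patients: "69 in custom made group, 69 in placebo group and 47 in usual care group". The Discussion adds that the pain figures were rescaled to the 0–10 NRS.

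**The concern.** The sentence pairs an effect size of 0.5 with 10.5 points and SD 21.5, and these do not match: with that SD, 0.5 is 10.75 points. Rounding an effect size upward lowers the required number. The loss allowance errs in the same direction, because removing the stated 10% from the randomised numbers leaves fewer patients than the same section says it needs.

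Custom made against placebo insole is the comparison that sets the size of the two larger arms. If its result is null or borderline, readers will judge it against the stated power, so that statement should follow from the figures printed beside it.

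**Working it through.** **Inputs** (Sample size section): difference 10.5; SD 21.5; power 0.80; two-sided alpha 0.05; 10% loss; 63 evaluable and 69 randomised per insole arm; 44 evaluable and 47 randomised in usual care. The Bonferroni correction is reserved for comparisons with usual care, so 0.05 applies here. Rescaling to 0–10 divides difference and SD alike and leaves their ratio unchanged.

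**Reproducing the plan's 63.** Per group, n = 2 × (1.960 + 0.842)² / d². With d = 0.5 this is 62.8, so 63 (64 by the t-test). The stated figure therefore comes from d = 0.5.

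**Using the stated difference and SD.** d = 10.5 / 21.5 = 0.488. The same formula gives 65.8, so 66 (67 by the t-test). Sidedness does not explain 63, since a one-sided test at 0.05 would need 52.

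**Loss to follow-up.**

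| Arm | Stated need | Need / 0.9 | Need × 1.1 | Randomised | Randomised × 0.9 |
|---|---|---|---|---|---|
| Custom made, placebo (each) | 63 | 70.0 | 69.3 | 69 | 62.1 |
| Usual care | 44 | 48.9 | 48.4 | 47 | 42.3 |

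The 69 looks like multiplication by 1.1, rounded down. The 47 follows from 44 by neither rule. Keeping 63, 63 and 44 after 10% loss would take 70 + 70 + 49 = 189.

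**Power for custom made against placebo, unadjusted two-group comparison.** Normal approximation: power = Φ(d × √(n/2) − 1.960). At n = 62, 0.488 × √31 = 2.719, and Φ(0.759) = 0.776. The t-test uses the noncentral t distribution.

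| Analysed per arm | Effect size | Normal | t-test |
|---|---|---|---|
| 63 | 0.500 | 80.1% | 79.5% |
| 63 | 0.488 | 78.3% | 77.6% |
| 62 | 0.500 | 79.5% | 78.9% |
| 62 | 0.488 | 77.6% | 77.0% |

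At 63 per arm, the rounding costs about 1.9 percentage points (80.1 to 78.3, or 79.5 to 77.6). Going from 63 to 62 costs a little over 0.6 more.

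**Difference detectable with 80% power at 62 per arm.** (1.960 + 0.842) × 21.5 × √(2/62) = 10.8 points by the normal approximation, and 10.9 by the t-test.

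**Number that would restore 80% for 10.5 points.** 66 / 0.9 = 73.3, so 74 randomised per insole arm; 67 / 0.9 = 74.4, so 75. The plan has 69, a shortfall of 5 or 6 per arm.

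**The case against.** *It is one-decimal rounding, shown openly.* 0.488 does round to 0.5, every input is printed, and 63 reproduces from 0.5. But the sentence claims power for 10.5 points at SD 21.5, and 63 is too few for that. Nor does accepting 0.5 rescue the 80%: after the stated loss, 62 per arm give 78.9% or 79.5%.

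*The loss allowance is immaterial.* For the insole arms this largely stands: 69 against 70 is one patient per arm. It is a minor contributor and not an equal cause. What remains is that the section contradicts itself on the numbers left after loss, most visibly with 47 and 44 in usual care.

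*The planned analysis is not an unadjusted two-group test.* This stands as a limit. The Data analysis section plans repeated-measures regression adjusted for at least age, gender, BMI and activity level, which could raise power. As an illustration only, if the covariates had a combined correlation of 0.27 with the outcome (an assumed value), 62 per arm would give about 80%; at 0.2 it would be 78.6%. The protocol gives no correlation, and its sample size takes no credit for adjustment.

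*The gap is small beside the uncertainty of an SD borrowed from another instrument.* True, and this limits the weight of the point. It does not make the printed power statement correct.

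**Conclusion.** The point holds. On the protocol's own figures and its own simple calculation, 69 randomised per insole arm with 10% loss give 77.0% (t) or 77.6% (normal) power for 10.5 points, 2.4 to 3.0 percentage points below the stated 80%. This assumes SD 21.5, equal insole arms, two-sided alpha 0.05 and exactly 10% loss. The shortfall is modest and does not undermine the trial, but the statement should be corrected.

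A reader might infer two stronger things that the document does not support:

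- That the trial itself has only 77% power. The figure belongs to the unadjusted calculation; the power of the adjusted repeated-measures analysis cannot be derived from what is given.
- That the stated inputs call for 74 + 74 + 49 = 197 patients. That sum takes the 44 in usual care as given, but 12 points with SD 21.5 in equal groups need 51 (normal) or 52 (t). The 44 reproduces only as the smaller arm of a 63-versus-44 comparison at unadjusted alpha 0.05 (80.4% by the t-test). No corrected total should be built on it.

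**What to change.** Keep 185 patients and restate the power in the Sample size section, for example:

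> With 69 per insole arm and 10% loss, about 62 per arm are analysed. In an unadjusted two-group comparison this gives about 77% power for 10.5 points (SD 21.5, effect size 0.49) and 80% power for about 10.9 points. Covariate adjustment and repeated measures may raise this.

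Apply attrition as n/(1 − 0.10). Then either give the evaluable numbers as 62, 62 and 42, or say that the randomised numbers fall slightly short of 63, 63 and 44.

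The cost is wording only. Recruitment, allocation and analysis are unchanged, and the stated power becomes slightly less favourable. The detectable difference moves from 10.5 to about 10.9 on the 0–100 scale, or 0.04 on the 0–10 NRS.

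### The usual-care arm is sized at an uncorrected alpha of 0.05, although the plan Bonferroni-corrects the comparisons with usual care; power for 12 points is then about 70%, not the implied 80%

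*Protocol article*

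**What the plan says.** All of the sizing is in the Sample size section of the protocol article. The starting values are "pain score 63.4 (SD 21.5), with a difference in pain score of 10.5" on a 0–100 scale, and the design settings are introduced with "it is estimated that with a power of 80 % and an alpha of 0.05 (two-sided". The effect size is given as 0.5, leading to "patients with a placebo insole and custom made insole with 63 patients in each study group".

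For custom made insole versus usual care the section expects a larger difference: "With a 12-point difference and identical means and SDs, a total of 44 patients are needed per group". Power and alpha are not restated there, so the natural reading is that the 80% and 0.05 carry over.

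The sentence that follows is "A Bonferroni correction will be performed for the secondary comparisons to the usual care group". The Data analysis section repeats this rule. Neither place gives the number of comparisons or the corrected alpha.

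After allowing for 10% loss, the arms are "69 in custom made group, 69 in placebo group and 47 in usual care group", 185 in total.

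**The concern.** An arm should be sized at the significance level at which its comparison will be tested. Here the sizing uses 0.05, and the testing rule in the adjacent sentence lowers that level. The two statements cannot both hold at 80% power and 12 points.

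A second flaw lies in the same sentence. The stated number per group cannot be recovered from the stated difference and SD with equal arms, so a reader cannot check it as written.

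At stake is how the usual-care result will be read. The Objectives section names usual care as a comparator in the primary objective, and the size of the usual-care arm (47) rests on this one calculation. If the true difference were 12 points, the chance of missing it would be about 30% rather than 20%. A non-significant result would be judged against more power than the design has.

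**Working it through.** **Inputs** (Sample size section): SD 21.5; differences 10.5 and 12; two-sided alpha 0.05; power 80%; arms 69, 69 and 47; loss 10%.

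**Assumptions** (not in the protocol): two corrected comparisons (custom made and placebo, each against usual care), so 0.05/2 = 0.025 each; three comparisons, 0.05/3 = 0.0167, as a sensitivity case; an unadjusted two-sample t-test.

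**1. The plan's own figures.** Normal formula, equal arms: n = 2(1.960 + 0.842)²/d² = 15.70/d².
- d = 0.5: 62.8, so 63 per group, as stated. The unrounded 10.5/21.5 = 0.488 would give 65.8, so the plan rounded the effect size up.
- d = 12/21.5 = 0.558: 50.4, so 51 per group (52 by t-test), not 44.
- d = 0.6, the same effect size rounded up to one decimal: 43.6, so 44 per group, as stated.

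The same formula with the same rounding therefore gives both 63 and 44. There is also a second route to 44: with the custom made arm fixed at 63 and d = 0.558, the t-test needs 44 in usual care (power 80.4%), while the normal approximation needs 42. Both routes use alpha 0.05.

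**2. What alpha 0.025 would require.** With 63 in the custom made arm and d = 0.558, 80% power needs 60 (normal) to 62 (t-test) evaluable usual-care patients, against the 44 stated.

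**3. Power of the planned arms.** SE = 21.5 × √(1/n₁ + 1/n₂), and the noncentrality is 12/SE. After 10% loss, 69 × 0.9 = 62.1 and 47 × 0.9 = 42.3, so 62 and 42.

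| Custom vs usual care | SE | 12/SE | alpha 0.05 | alpha 0.025 | alpha 0.0167 |
|---|---|---|---|---|---|
| 63 vs 44 | 4.224 | 2.841 | 80.4% | 71.4% | 65.8% |
| 62 vs 42 (10% loss) | 4.297 | 2.793 | 79.0% | 69.7% | 64.0% |
| 69 vs 47 (no loss) | 4.066 | 2.951 | 83.3% | 75.1% | 69.9% |
| 44 vs 44 (equal arms, as worded) | 4.584 | 2.618 | 73.5% | 63.2% | 57.2% |

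Power is from the noncentral t distribution. The normal approximation is about 1 to 2 points higher: for 62 vs 42 at 0.025 it gives Φ(2.793 − 2.241) = 70.9%.

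**4. Detectable difference.** For 62 vs 42 at 0.025 and 80% power, the normal approximation gives (2.241 + 0.842) × 4.297 = 13.2 points. The t-test gives 13.4. The plan uses 12.

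**The case against.** Four points can be made for the plan.

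*The analysis is not a two-sample t-test.* Data analysis specifies covariate-adjusted regression for repeated measurements, which can gain power. If covariates correlated 0.45 with the outcome (an assumption), the SD would shrink by √(1 − 0.45²) and power for 62 vs 42 at 0.025 would be about 80%; at a correlation of 0.3 it would be about 74%. This stands as a caveat on the percentages. It does not rescue the stated figure, because the calculation claims no such gain and the article gives no correlation.

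*The number of corrected comparisons is not stated.* True, so 0.025 is an assumption. Two is the natural reading of the plural in a three-arm trial. Three makes the shortfall larger.

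*The comparison is called secondary, and 80% is not restated for it.* Both are true. But the plan sized an arm for this comparison, and 44 reproduces at 80% and 0.05.

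*The figure of 44 is coherent as written.* A reader might infer that 44 can arise only against 63 custom made patients and that the words per group are a slip. The documents do not support this. Equal arms with the effect size rounded to 0.6 give 44 per group by the same formula that gives 63. The text does not settle which route was used, so the sentence should not be rewritten as 44 against 63.

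**Conclusion.** The point holds. The usual-care size of 44 (47 with loss) was calculated at two-sided 0.05, while the plan tests those comparisons at a stricter level. For 12 points and SD 21.5, power is about 70% after the planned loss and 75% with no loss, assuming two comparisons and an unadjusted t-test. With three comparisons it is about 64% after loss. Separately, 44 per group does not follow from 12 and 21.5 with equal arms, which need 51 to 52.

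Two stronger readings should be resisted. The 70% is not an established property of the trial, because it rests on the assumptions just named. Nor does the shortfall carry over to the cost-effectiveness objective: Data analysis handles that with costs and recovery, bootstrap intervals and an acceptability curve, not with the Bonferroni-tested pain difference. The custom made versus placebo comparison is not affected by this correction.

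**What to change.** Change the Sample size section as follows:

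- State how many comparisons with usual care are corrected and the resulting alpha, and use the same statement under Data analysis.
- Use the unrounded effect size, 12/21.5 = 0.558.
- Replace the sentence giving 44 per group with the power of the planned arms. For example: with 62 custom made and 42 usual-care patients analysed and a two-sided alpha of 0.025, power is about 70% for a difference of 12 points and 80% for about 13.4 points.
- Add that this is an unadjusted two-sample approximation that takes no credit for covariate adjustment or repeated measures.

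The example figures assume two comparisons and must be recalculated if the number differs. The cost is wording only. No extra patients and no change of analysis are asked for, but the stated power becomes less favourable.
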